##### Credibility/expectancy questionnaire, adapted from Devilly & Borkovec (2000) [53]

3.3.4.2

Before the intervention or control task, participants will rate the extent to which they consider the intervention/control task credible via five items, on an 11-point scale (from 0 to 10). For example, one item asks participants, “How successful do you think the task will be in preventing/reducing your intrusive memories?”. All items will be summed; a higher score indicates greater credibility. The credibility/expectancy questionnaire possesses high internal consistency (α = 0.84 - 0.85) and good test–retest reliability (r = 0.83) for the whole scale [53].

##### Subjective units of distress (SUDS)

3.3.4.3

A single item that asks participants to rate their current level of distress on an 11-point scale from 0 (“no distress at all”) to 10 (“worst imaginable distress”), to be completed three times during the intervention/control procedure.

##### List of intrusive memories (only intervention arm)

3.3.4.4

As part of the intervention, participants will list a brief description of the content of their intrusive memories in six free response fields. More than six responses can be entered if necessary.

##### Adherence to intervention/control task instructions

3.3.4.5

Adherence to the intervention/control task instructions will be assessed via three multiple choice items asking participants the most important thing they did before completing the task, what they mainly focused on during the task, and the approximate amount of time they spent completing it. An additional single item asks participants to rate the extent to which they agree with the statement ‘During the past 20 min, I followed the instructions’ on an 11-point scale (from 0 “not at all” to 10 “extremely”). For the intervention group, two additional items ask participants to rate the vividness of their trauma memory before playing Tetris, and whether they turned off “ghost piece” during game play.

##### Number of booster sessions delivered by researcher

3.3.4.6

The number of booster sessions delivered by a researcher will be recorded in the platform, along with the date of each booster session.

##### Number of days/nights at work during week of intrusion monitoring

3.3.4.7

Two separate items asking participants how many days/nights they had worked during the previous week.

#### Feedback to assess acceptability and improve materials and procedures for implementation

3.3.5

##### Feedback questionnaire about participation

3.3.5.1

At 1-month follow-up, participants will be asked to provide four ratings about the task they completed (intervention or control): i.e., how simple it was to complete, how upsetting it was, how acceptable they found it, and whether they would recommend it to a colleague or friend who has had a similar experience, all on a scale of 0 (not at all) to 10 (very much). Participants will also be asked whether they have done the task on their own (yes/no; if they say yes they are asked to indicate how many times), and whether they have received any treatment as a result of the traumatic event since they commenced participation in the study (yes/no). If participants indicate they have received any treatment, they will be asked to describe it. Participants will also be asked if they have told others (e.g., friends, colleagues) about the task (yes/no), and also asked if they have any other comments.

##### Open ended feedback questions

3.3.5.2

After completing their randomly assigned task on Day 1, participants will complete five free response questions about the feasibility of the task, the instructions, and their experience of doing the task. Additionally, at each follow-up time point, participants will be asked to provide any comments they have about the study procedure, or indicate how the study could be improved in the future.

### Adverse events

3.4

We will screen for adverse events (at 1-week, 1-month, 3-month, and 6-month follow-ups) using a brief self-report form (‘Have you had any health problems since the last contact’ [yes/no], if yes is answered: ‘Briefly describe which:‘) used by our local clinical trials unit (KTA).

Any adverse events reported (whether spontaneously reported by the participant to study personnel or during follow-ups in the electronic platform SMART-TRIAL) will be registered in an adverse event log. Adverse events will be classified as serious or not. Adverse events will be assessed for severity (mild, moderate or severe) and relationship to intervention (not related, unlikely, possible, probable, definite) by the Principal Investigator. Any actions taken will be logged.

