*Explanation of booster sessions for persistent intrusions or for different intrusions on the list.* After the first ‘dose’, the intervention can be repeated independently for the remaining intrusive memories on the participant's list, and/or if the targeted memory were to persist. Thus, in this last phase of the guided session, the researcher will explain how to use the intervention in a self-administered way; e.g., encourage participants to use it after they experience an intrusive memory in daily life (i.e., when an image comes to mind involuntarily) if it is convenient to do so. It may be the case that in many instances, it is not feasible for participants to use the intervention immediately after experiencing an intrusion (e.g., if they are at work). Accordingly, another option for participants who experience persistent intrusions would be for them to find a more convenient time when they can *deliberately* bring the intrusive image to mind (via the memory reminder cue procedure). Whether the memory is involuntarily or deliberately retrieved, participants will be encouraged to next play Tetris with active mental rotation for at least 20 min continuously. They are not expected to do the task procedure each and every time they have an intrusion, rather it is participants' choice as to how they can flexibly fit boosters into their daily life. We also note that the intervention is to be conducted once for each different intrusive memory (i.e., from participants' *list of intrusive memories*) – thus if the same memory intruded 10 times, the booster would be done once. However, if two different memories intruded, two boosters would be needed. If a given memory continues to persist, then a booster could be done again. Participants can also receive researcher-guided ‘Booster doses’ (i.e., with remote researcher support, see 2.6.5).

*Duration of the intervention.* The guided intervention task procedure conducted with researcher support will be approximately 25 min in duration; when self-administered the intervention takes c. 20 min.

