##### Adverse events

3.3.4.1

A free response question in which participants indicate whether they have experienced any health issues since their last contact with the study team.

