As the next step in this line of investigation, we have here outlined the protocol for an RCT: the first investigation of the effects of a blended digital and remotely-delivered form of this brief cognitive task intervention on the number of intrusive memories after traumatic event(s) in healthcare staff working during the COVID-19 pandemic. The intervention will be delivered using a blend of various digital tools with guided (remote) support from a researcher with the aim of fitting study procedures around the reality of staff's working lives under the pandemic. This format confers multiple practical advantages: it is brief, can be completed anywhere, and is repeatable independently by staff during ongoing/further trauma exposure. Further, from the outset, all aspects of the conduct and implementation of the trial have been developed in close collaboration with experts by lived experience – that is, healthcare staff working at the frontline during the pandemic. Another advantage of the intervention for this population is that it does not require discussion of the trauma in detail, and thus participants do not need to become significantly distressed. Moreover, it is notable that across all of the studies evaluating this intervention conducted to date, no adverse events related to study procedures have been reported.

Raising an important final consideration, we emphasize the unprecedented context in which this trial is being carried out. Since the conception and commencement of the trial, the severity and impact of the COVID-19 pandemic in Sweden escalated to an extent that could not have been foreseen. At the time of submitting this manuscript (May 2021), Sweden was at crisis point – having just recorded the highest number of daily COVID-19 cases in Europe, and with hospital resources significantly overstretched [63]. It is plausible that the increasing severity of this situation may result in an increase in the number of intrusions, and the degree of intrusion-related distress, reported by participants enrolled in the trial as it progresses over time. At the time of submitting the revised version of this manuscript, and after the vaccination program in Sweden rolled out, there had been a drop in the number of COVID-19 cases.

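### Section 3.4 states no link between adverse event reporting and the symptom scores already collected, so individual worsening is logged only if the participant volunteers it

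*Protocol article*

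**What the plan says.** Section 3.4 sets out how adverse events are found: "We will screen for adverse events (at 1-week, 1-month, 3-month, and 6-month follow-ups) using a brief self-report form". The question is "Have you had any health problems since the last contact", answered yes or no, with a short description if yes. Section 3.3.4.1 lists the same item as "A free response question in which participants indicate whether they have experienced any health issues since their last contact with the study team". Section 3.4 also admits spontaneous reports, since the log is to hold "Any adverse events reported (whether spontaneously reported by the participant to study personnel or during follow-ups in the electronic platform SMART-TRIAL". Logged events are classed as serious or not, then graded by the Principal Investigator for severity and relationship to the intervention.

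The intervention (section 2.5.3) asks participants to recall a trauma image deliberately before the gameplay. It is then meant to be used alone: "After the first ‘dose’, the intervention can be repeated independently for the remaining intrusive memories". Distress during the Day 1 session is rated on SUDS (section 3.3.4.3), "to be completed three times during the intervention/control procedure". SUDS is filed under procedure assessments.

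The Discussion (section 6) says that across earlier studies of this intervention "no adverse events related to study procedures have been reported".

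**The concern.** If deliberately reactivating a trauma image harmed someone, the likely signs would be more intrusions, worse PTSD symptoms or distress that does not settle. The trial measures all three but files them as efficacy, procedure or acceptability data. The instrument that feeds the adverse event log asks about health problems in general.

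That question fits poorly with this population. Under section 2.2, everyone enrolled already has distressing intrusive memories, at least two in the week before inclusion. A participant who has just rated these symptoms on dedicated scales has little reason to list them again as a health problem. The log is likely to collect incidental illness more readily than worsening of the condition under treatment.

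What is at stake is what the trial can say about harm. A log with few or no related events would be weak evidence that nobody worsened, because the article states no systematic check for it.

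**Working it through.** The plan gives no figure on this point, so the check sets the relevant sections side by side.

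| Source | When (Table 1 and section 3) | Arms | Role in the article | Stated route to the adverse event log |
|---|---|---|---|---|
| Health question | D8, D29, D85, D169 | both | adverse events | direct, if answered yes |
| Spontaneous report | any contact | both | adverse events | direct |
| Diary count | Weeks 0, 1, 5 | both | primary (Week 5), secondary (Weeks 0, 1) | none |
| IES-R intrusion | baseline, D8, D29, D85, D169 | both | secondary | none |
| PCL-5 short version | baseline, D8, D29, D85, D169 | both | secondary | none |
| SUDS | three times on Day 1 | both | procedure assessment | none |
| Rating of how upsetting the task was | 1 month | both | acceptability feedback | none |

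1. **Same visits, separate purposes.** The IES-R and PCL-5 fall on the same four follow-up days as the health question. The data needed to detect individual worsening are therefore in hand whenever adverse events are asked about, but no section joins the two.

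2. **Timing around the primary outcome.** The Week 5 diary runs from D29 to D35. The health question is asked at D29 and next at D85, which is 85 − 35 = 50 days after that diary ends. A rise in intrusions during Week 5 depends on recall over that interval or on a spontaneous report.

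3. **Where a signal is seen, no harm step is stated.** Section 2.5.5 has researchers watch the intervention arm's Week 1 diary and contact participants with persistent intrusions about boosters. It does not say whether a rise from Week 0 is also recorded as a possible adverse event.

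4. **Arm comparisons do not answer the question.** Section 4.1 plans between-group comparisons. Suppose a share p of an arm worsens by an average w and the rest improve by an average b. The arm's mean improves whenever (1 − p) × b > p × w. That can hold with p well above zero, so a favourable mean does not show that few participants worsened.

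5. **Counts are widely spread.** The pilot control arm in section 4.2 had mean 2.89 and SD 6.43, a ratio of 6.43 / 2.89 = 2.2. With spread of this order, a worsening minority is hard to see in a group summary. This is variation between people, so it does not by itself give the margin needed for change within a person.

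**The case against.** The strongest reply is that the article does not exclude symptom worsening from the log. Nothing limits the health question to physical illness, its follow-up is free text, and the respondents are healthcare staff. Spontaneous reports count. There are open comments at every follow-up (section 3.3.5.2), a treatment question at 1 month (section 3.5) and roughly daily review of incoming diary data (section 2.5.6). All of this stands. A reader might infer that harm is counted only from the questionnaire, or that worsening can never enter the safety result. The documents support neither reading.

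One qualification applies. Researcher-initiated booster contact is for the intervention arm only (section 2.5.5). It gives that arm more occasions for spontaneous reports, and it can shorten a recall window defined by the last contact. It adds a route, but not an even-handed one.

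Second, the harmful direction is tested: the diary, IES-R and PCL-5 are randomised outcomes, so net worsening of an arm would appear. This also stands, but it does not cover individuals.

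Third, deterioration thresholds and harm tables often belong in a SAP, which is not shown. That is fair for the margins and the layout. Ascertainment, however, is protocol content, and section 3.4 gives it down to the wording of the question.

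Fourth, a reader might take section 6 as resting wider use of the intervention on a safety claim. It does not: dissemination is tied there to fewer intrusive memories, and the remark about adverse events concerns earlier studies.

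**Conclusion.** The point holds in a limited form. As written, adverse events come from one general question plus spontaneous reports, with no stated link to the diary, IES-R intrusion, PCL-5 or SUDS data. Worsening of target symptoms in an individual reaches the log only if volunteered, and arm-level comparisons can mask it.

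No numerical size can be attached. The documents give no rate of deterioration and no rate at which participants would volunteer it, so any count of missed cases would be pure assumption. The efficacy conclusions are unaffected.

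The judgement rests on two assumptions: that the unseen full protocol or SAP does not already define such a summary, and that participants under-report known symptoms when asked about health problems. The first can be checked directly. The second is plausible given the entry criteria but is not shown by the documents. This is a worthwhile low-cost improvement, not a defect in the trial's main result.

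**What to change.** Add to section 3.4 a descriptive harm table giving number and percentage by arm with individual deterioration from baseline:

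- diary count in Week 1 and in Week 5, each against Week 0;
- PCL-5 and IES-R intrusion at each follow-up, against baseline.

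Each criterion needs a margin larger than ordinary fluctuation, fixed in the SAP before unblinding. The PCL-5 margin at 1 week needs care, because section 3.2.4 uses a one-week recall period there and one month otherwise. Give the denominator and the number missing by arm for each cell, since people who worsen may also stop responding.

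Report the change in SUDS across the session by arm descriptively. Counting any rise as harm would be too loose: one point on the 0 to 10 scale would qualify, and only the intervention arm is asked to recall a trauma image.

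Base any statement about absence of harm on this table together with the adverse event log. If the full protocol or SAP already provides this, a cross-reference in section 3.4 is enough.

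The cost is a few sentences and one table, with no new data and no change to participants' care. The drawback is that some worsening will be natural fluctuation or follow new trauma at work, so the percentages must be read against the control arm and not as event rates caused by the task.

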### Monitoring of additional treatments

3.5

Participants will be asked at baseline whether they have ever been diagnosed with and have ever received treatment for any mental health problem/s (including depression, anxiety or PTSD).

At one-month follow-up participants will be asked (on the Feedback Questionnaire about participation) whether they have received any treatment since they did the task for the first time (e.g., psychological treatment or medication) because of the traumatic event/s. If participants indicate they have received treatment, they will be asked to provide details in an open-ended response.

## Statistical considerations

4

### Data analysis

4.1

This is a between-subjects design in which we are interested in between-group comparisons post-intervention. The primary outcome (number of intrusive memories) is based on count data, which is not typically normally distributed [54]. We expect large variability in the number of intrusive memories reported across participants, which may also vary as the pandemic progresses, and we seek to take into account baseline rates.

Main analyses will be based on intention-to-treat; i.e., will utilize available data from all randomized participants. A statistical analysis plan (SAP) will be preregistered (e.g., on the Open Science Framework, OSF) prior to data analysis. The statistician conducting the analyses will be blind to condition (e.g., groups will be labelled only as ‘A’ and ‘B’ in the analysis data file). Analyses will be conducted in appropriate statistical software and we aim to make data analysis code publicly available (e.g., on the OSF).

Corrections for multiple testing are not required for the primary outcome, which includes only one comparison at a single time-point. We also plan to explore data such as participants’ qualitative responses regarding their experience in the study and impressions using the intervention/control task. Numerical outliers will be removed in cases where data was not a legitimate part of the data generation process (e.g., errors in data entry, invalid or implausible responses). Missing data will be addressed using multiple imputation. Sensitivity analyses will be conducted to assess the potential impact of missing data on the results (recommended by the National Research Council Panel on Handling Missing Data in Clinical Trials [56]).

### Sample size estimation

4.2

We anticipate recruiting a total of 164 participants (*n* = 82 per condition) in order to detect a medium effect, based on findings for the number of intrusive memories at Week 5 in our pilot study, mean intervention = 0.28 (SD = 0.57) versus mean control = 2.89 (SD = 6.43) [25], and factoring in potential attrition. Based on this between group difference (*d* = 0.57, equivalent of ∼0.5 standard deviation units), power of 90% and alpha of 0.05, we would require 65 participants per group (130 completers in total, see also our earlier planned study [26]). The attrition rate of 12.2% in the pilot trial [25] would suggest aiming to recruit 146 participants in the current trial. However, given the challenges of the current COVID-19 pandemic and their potential to compromise retention, we have opted to take a more conservative approach and estimate an attrition rate of 20%; accordingly, our estimated enrolment would be 164 participants. If, for example attrition is lower than expected we may well enroll fewer than the estimated 164 participants. Decisions will be made with statistical and data monitoring input and other individuals/groups overseeing the trial.

### Data management

4.3

Included participants will be pseudonymized (coded) by assigning a unique numeric identifier. Participant data will be treated confidentially and the system used for data collection and study handling is secure and password-protected. Self-report data will be entered by participants directly into an electronic Case Report Form (eCRF) form (encrypted secure and GDPR compliant electronic data collection platform); other data (e.g. eligibility criteria, number of booster sessions) is entered into the eCRF by the researchers. Any digital documents that include identifying information (e.g., the electronic signed Informed Consent Forms/recordings) will be stored separately from participant data on a secure password protected university server; any paper documents will be stored in a locked fireproof safe. The principle investigator will have continued access to the final dataset. Participants provide their informed consent that their pseudonymized data may be made available for secondary research (e.g., via the OSF). We aim to share pseudonymized data according to the FAIR Guiding Principles (i.e., such that data is findable, accessible, interoperable, and reusable) [58]. More details regarding data management will be specified in a data management plan created using the ‘DMPonline’ system.

## Ethical considerations

5

The study will be performed in accordance with the study protocol and the ethical principles of the World Medical Association (WMA) Declaration of Helsinki (as amended by the 64th WMA General Assembly, Fortaleza, Brazil, October 2013) [59], and aims to follow Good Clinical Practice (GCP) guidelines.

The study has received ethical approval from the Swedish Ethical Review Authority (approval no. 2020–03085). Modifications to the protocol (e.g., to include an audio-recorded verbal informed consent process; adapt inclusion criteria; adapt advertising materials; add additional measures) have been approved (amendments no. 2020–06399, 2020–06600, 2021–01651, 2021–03691) and we plan to request approval as necessary for any modifications in the future.

The study was preregistered in the Clinical Trials Registry (clinicaltrials.gov) on 07-07-2020 (no. NCT04460014). This protocol aims to follow the Standard Protocol Items: Recommendations for Interventional Trials (SPIRIT) guidelines [60]; see checklist in Appendix 1. The trial sponsor is Karolinska Institutet, Sweden (contact information: [contact]). The study includes a trial steering committee chaired by [name] (independent member). The advisory committee at project start includes [name], [name] [name], and [name] [name] (representatives of our participant group). An independent clinical trials unit (Karolinska Trial Alliance, KTA) will monitor the study (e.g. ethical considerations, study protocol, primary outcome data) to promote compliance with Good Clinical Practice (GCP). Staff on the study will receive training in GCP.

Participants will provide their informed consent remotely (as attested by scanned paper consent form or audio-recorded verbal consent) prior to commencing the study. Prior to giving consent, participants will receive information about the nature of the study, its purpose, expected duration, the benefits, and risks involved. Participants will be informed that their participation is voluntary and that they can withdraw their consent at any time without providing a reason. Participants will receive this information in written form (i.e. via email or downloaded from the study webpage) and will be given as much time as they need to read study information materials and consider study participation. Prior to taking informed consent, the investigator or a member of the research team will answer any questions about this information or any aspect of study participation via phone/video call. In this phone/video call eligibility for study participation will be assessed as well.

Our ethical procedures for remote recruitment during the pandemic have been developed in collaboration with representatives of our participant group (including practicing nurses, ambulance nurses, nurse researchers) and were piloted prior to commencing the RCT [15].

We plan to communicate trial results as publications in peer-reviewed scientific journals, through presentations at national and international scientific conferences and internal meetings at the hospital/university. We plan to follow internationally recognised authorship guidelines (e.g. guidelines of the International Committee of Medical Journal Editors, ICMJE).

